# Relationship between plaque composition by virtual histology intravascular ultrasound and clinical outcomes after percutaneous coronary intervention in saphenous vein graft disease patients: study protocol of a prospective cohort study

**DOI:** 10.1186/s12872-018-0975-1

**Published:** 2018-12-12

**Keywords:** Saphenous vein graft disease, Virtual histology intravascular ultrasound, Percutaneous coronary intervention, Major adverse cardiac events

## Abstract

**Background:**

Plaque composition and morphologic characteristics identified by virtual histology intravascular ultrasound (VH-IVUS) can determine plaques at increased risk of clinical events following percutaneous coronary intervention (PCI) among coronary artery disease (CAD) patients. However, there have been few studies to investigate the relationship between plaque composition of saphenous vein graft (SVG) by VH-IVUS and clinical outcomes in patients with saphenous vein graft disease (SVGD) undergoing PCI. The purpose of this study is to determine whether plaque components and characteristics by VH-IVUS can predict major adverse cardiac events (MACEs) among SVGD patients undergoing PCI.

**Methods/design:**

This is a prospective cohort study conducted in Tianjin Chest Hospital, China. Participants with SVGD referred for PCI will be invited to participate in this study, and will be followed up at 1, 6, 12, 24 and 36 months post-PCI to assess clinical outcomes.

The planned sample size is 175 subjects. We will recruit subjects with SVGD scheduled to receive PCI, aged 18–80 years, with a history of previous coronary artery bypass graft (CABG) surgery more than 1 year ago, and willing to participate in the study and sign informed consent.

The composite primary study endpoint is the incidence of MACEs after PCI for SVGD, including death from cardiac causes, non-fatal myocardial infarction, unplanned target lesion revascularization (TLR) and target vessel revascularization (TVR). The primary outcome analysis will be presented as Kaplan-Meier estimates and the primary outcome analysis will be carried out using a Cox proportional hazards regression model.

**Discussion:**

Once the predictive values of plaque components and characteristics by VH-IVUS on subsequent clinical outcomes are determined among SVGD patients undergoing PCI, an innovative prediction tool of clinical outcomes for SVGD patients undergoing PCI will be created, which may lead to the development of new methods of risk stratification and intervention guidance.

**Trial registration:**

The study is registered to ClinicalTrials.gov (NCT03175952).

## Background

Coronary artery bypass graft (CABG) surgery is a widely used surgical procedure to treat coronary artery disease (CAD). Saphenous vein grafts (SVGs) are commonly used in CABG due to the advantage of availability, although the patency rates of SVGs are lower than that for arterial grafts [1–3]. However, about 40–50% of the SVGs will be occluded within 10 to 15 years after CABG surgery [1, 4, 5]. Newly developed atherosclerosis is the major reason for long-term poor prognosis [3]. SVG disease (SVGD), defined as a stenosis of 50% or more of the SVGs excluding distal anastomotic occlusion, has become an important cause of morbidity and mortality for CAD patients after CABG surgery [6, 7].

Both repeat CABG and percutaneous coronary intervention (PCI) are available treatment options for the management of SVGD [8–10]. Due to increased morbidity and mortality associated with patients undergoing repeat CABG, SVG PCI is the preferred therapeutic option to restore vessel patency and improve symptoms for patients with SVGD [11–13]. PCI in patients with prior CABG comprises up to 6% of the total PCI performed in the United States [14]. However, because of accelerated intimal proliferation and hyperplasia in venous conduits, SVG PCI is associated with increased risk of late failure and worse outcomes compared with native coronary artery interventions [15, 16]. Previous studies have shown that the incidence of major adverse cardiac events (MACEs) in patients who undergo bypass-graft PCI is significant higher than that in patients with native coronary artery PCI [17, 18]. It would be of particular interest to identify patients with poor prognosis after SVG PCI, which can be used for risk stratification and intervention guidance.

In recent years, intravascular ultrasound (IVUS) has been developed to identify vulnerable atherosclerotic plaques at high risk for coronary events. It was found that plaque characteristics (i.e., plaque burden, multiple plaque ruptures, lipid pool-like image and minimum luminal area) may be associated with no reflow phenomenon after PCI [19–22]. However, IVUS imposes limitations on identifying specific plaque components. Virtual histology-IVUS (VH-IVUS) is most widely used as it can assess both plaque composition and morphologic characteristics. VH-IVUS utilizes spectral and amplitude analysis of IVUS radiofrequency data to characterize plaque components, also suggesting the potential to identify vulnerable lesions [23, 24]. Moreover, several studies have demonstrated the independent relationship between VH-IVUS–defined plaque classification or plaque composition and MACEs [25, 26].

Considering similar pathophysiological mechanisms for CAD and SVGD, we hypothesized that plaque characteristics of SVG assessed by VH-IVUS might be associated with long-term clinical outcomes. However, data on plaque composition of SVG and its predictive values for clinical outcomes are still limited [27]. Thus, we sought to investigate the relationship between plaque composition of SVG by VH-IVUS and clinical outcome in SVGD patients undergoing PCI, which could identify morphologic features that are predictive of post-PCI MACEs.

## Methods and design

### Study design and setting

The study is a prospective cohort study conducted in Tianjin Chest Hospital, Tianjin city, China. Patients with SVGD referred for PCI are invited to participate in the study and VH-IVUS is performed in culprit SVG before and after PCI. Patients are recruited consecutively by surgeons at the Cardiology Department of Tianjin Chest Hospital. These subjects will be followed up at 1, 6, 12, 24 and 36 months post-PCI to assess clinical outcomes. The flow diagram of the study and the detailed study procedures are illustrated in Fig. 1.

**Fig. 1 Fig1:**
[figure not shown]
Study flow chart

### Participants

The patients to be included in the study should meet all of the following criteria: (1) aged 18–80 years; (2) a history of previous CABG surgery more than 1 year ago; (3) diagnosed as SVGD which is defined as at least one SVG ≥50% diameter stenosis; (4) plans for receiving PCI using drug-eluting stents; (5) willing to participate in the study and sign informed consent.

Patients will be excluded from the study if any of the following criteria is met: (1) acute myocardial infarction within the previous 7 days; (2) having any contraindication to aspirin, clopidogrel, heparin or stainless steel; (3) impaired renal or hepatic function; (4) history of cerebral stroke or ischemic cerebrovascular disease within 3 months; (5) history of gastrointestinal bleeding or hemoptysis in the previous 4 weeks; (6) pregnant or breastfeeding; (7) vasculitis or other non-atherosclerotic CAD; (8) other major illnesses that would expose the participant to unexpected risk: hematologic disorder, malignancy, etc.

Participants can withdraw from the study at any time without any adverse outcome on subsequent treatment; the reasons for withdrawal will be recorded. The investigator can also exclude a participant from the study for reasons including serious adverse events or poor compliance with research protocol.

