### Baseline assessment and follow-up

After receiving written informed consent, clinical staff will collect demographic and clinical characteristics from all participants. Medical records will be reviewed and related clinical information will be extracted. The data to be collected at baseline include demographic characteristics, medical history (diabetes mellitus, hypertension, hyperlipaemia, stroke, arrhythmia, previous myocardial infarction, PCI or CABG surgery, and medicines for cardiovascular disease), physical examination, clinical presentation (vital signs at hospital admission, onset time of chest pain, duration of chest pain, cardiac function with Killip classification), and smoking history. Cardiac color ultrasound, coronary angiogram, pre- and post-PCI VH-IVUS and 18 lead ECG will be done and used for checking inclusion/exclusion criteria. In addition, blood samples will be collected for laboratory testing, including routine blood, blood biochemistry, fasting glucose, coagulation function, homocysteine, cardiac damage markers (lactic dehydrogenase, creatine kinase, B-type natriuretic peptide, hydroxybutyrate dehydrogenase, troponin H, myoglobin), and inflammatory factors.

Eligible participants will be hospitalized for PCI treatment. In the therapy phase, patients will receive PCI for SVGD using drug-eluting stents. Operation notes (operation date, bleeding volume, medication), thrombolysis in myocardial infarction (TIMI) flow, corrected TIMI frame count (CTFC) and adverse events will be recorded in detail.

All subjects will be followed up at 1, 6, 12, 24 and 36 months after surgery, with MACEs and adverse events assessment collected at each time by clinic visits or telephone interview.

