### Study endpoints

The composite primary study endpoint is the incidence of MACEs after PCI for SVGD, including death from cardiac causes, non-fatal myocardial infarction, angina pectoris, target vessel revascularization (TVR) and hospitalization for heart failure.

Secondary endpoints are defined as: (1) the occurrence of the slow/no reflow, which is defined as thrombolysis in myocardial infarction (TIMI) grade 0, 1, or 2 flow within 24 h after SVG-PCI, despite successful treatment of the vessel obstruction; (2) myocardial infarction is defined as the onset of chest pain in combination with new, typical changes in the electrocardiogram and biochemical evidence of myocardial necrosis; (3)TVR is defined as a new revascularization procedure in the target vessel; (4)successful reperfusion is defined as TIMI flow grade 3 and less than 50% residual stenosis of SVG.

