### Statistical analysis

Analyses will be made using SAS statistical software (version 9.3) by researchers at the Peking University Clinical Research Institute. Continuous variables will be expressed as mean ± standard deviation or median ± interquartile range (IQR), and t-test or Wilcoxon rank sum test will be used to compare the difference between groups. For categorical variables, the chi-square test/ Fisher’s exact test will be performed. Time-to-event data (MACEs in 3 year after PCI) will be presented as Kaplan-Meier estimates and the primary outcome analysis will be carried out using univariate and multivariate Cox proportional hazards regression models. The ideal cut-off of quantitative indexes of VH-IVUS and the diagnostic accuracy will be determined by the receiver-operating characteristic curve (ROC). A *p*-value < 0.05 will be considered statistically significant in all analyses.

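### The investigator may exclude enrolled patients after a serious adverse event or for non-compliance, which permits outcome-related censoring and conflicts with following every subject to 36 months

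*Protocol article*

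**What the plan says.** In the Protocol article, the Participants section first lists the eligibility exclusions. It then allows participants to withdraw, in which case "the reasons for withdrawal will be recorded". After that it adds a separate power for the study side: "The investigator can also exclude a participant from the study for reasons including serious adverse events or poor compliance with research protocol". Because it follows the withdrawal sentence and stands apart from the eligibility list, it acts after enrolment. It concerns leaving the study, not stopping a treatment.

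The Study endpoints section defines the primary composite as MACE "including death from cardiac causes, non-fatal myocardial infarction, angina pectoris, target vessel revascularization (TVR) and hospitalization for heart failure". The Abstract lists a different composite, but cardiac death and non-fatal myocardial infarction are in both.

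The Baseline assessment and follow-up section states: "All subjects will be followed up at 1, 6, 12, 24 and 36 months after surgery". Each of these contacts, in person or by phone, is to gather endpoint and safety events. Under Statistical analysis, MACE over 3 years is shown by Kaplan-Meier estimates and "the primary outcome analysis will be carried out using univariate and multivariate Cox proportional hazards regression models".

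The article does not define a serious adverse event, exempt endpoint events from the exclusion rule, or say whether an excluded patient is still contacted or whether data up to exclusion are kept.

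**The concern.** The trigger for exclusion overlaps the outcome. Cardiac death, non-fatal infarction and heart-failure hospitalization are endpoint components and, as the term is normally used, serious adverse events. Other serious events plausibly share risk factors with MACE, and non-compliance may do so too (an inference, not stated in the article). Kaplan-Meier and Cox methods need censoring that carries no information on prognosis given the covariates, and this rule permits the opposite.

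Three things are at stake: an understated MACE incidence, the loss of some of a small number of events, and possible distortion of the plaque–MACE association. An analysis plan can define analysis sets, but it cannot recover follow-up that was never collected after a patient was excluded. The rule also cannot stand beside the statement that all subjects are followed to 36 months.

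**Working it through.** **1. The plan's own figure.** Inputs from the Sample size section: plaque-and-media area 2.9 (SD 1.7) mm² with MACE and 1.9 (SD 1.5) mm² without, MACE incidence 20%, drop-out 20%, power 80%, two-sided 0.05. With a 1:4 ratio and unequal variances:

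- n(MACE) = (1.960 + 0.842)² × (1.7² + 1.5²/4) / 1.0² = 27.1, rounded up to 28
- total = 5 × 28 = 140; 140 / 0.8 = 175, an exact match

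The arithmetic is sound. It delivers 28 events only if loss is unrelated to outcome: 175 × 0.20 = 35 expected events, and 35 × 0.8 = 28.

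**2. If excluded patients are censored.** The article gives no exclusion rate, so this is a simulation on assumed inputs: 140 patients, 20% MACE at 3 years, a normally distributed plaque index with log HR 0.53 per SD (HR 1.7), shared log-normal frailty with SD 0.7, and other serious events with 3-year incidence 15% or 30% that share the frailty and the index. Every patient with such an event is excluded and censored at that time. I re-ran it (3,000 runs per setting); ranges show the spread between separate runs.

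| | No exclusion | 15% | 30% |
|---|---|---|---|
| MACE events | 28 | about 25 | 21–22 |
| Kaplan-Meier incidence | 20% | about 19% | about 18% |
| Mean log HR | about 0.50 | 0.49 | 0.47–0.48 |
| Loss of power (points, from 71–73%) | – | 6–10 | 11–17 |

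On the hazard-ratio scale, exp(0.50) = 1.65 against exp(0.47) = 1.60. The crude proportion falls further, to 24.7/140 = 17.6% and 21.5/140 = 15.4%, but it ignores the censoring and is not the plan's estimator.

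If only one such patient in four is excluded, events are 26–28, Kaplan-Meier incidence is 19.5–19.9% and power is about 70%, which is hardly distinguishable from no exclusion.

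**3. If excluded patients' data are removed altogether.** In the same simulation about 21 (15%) or 16 (30%) events remain, and power is about 54% or 38%. A second view uses the plan's own formula, power = Φ(1.0 / √(1.7²/n + 1.5²/112) − 1.960), with n MACE patients left and 112 without MACE:

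| MACE patients removed (assumed) | n left | Power | Apparent incidence |
|---|---|---|---|
| 0 | 28 | 81.3% | 28/140 = 20.0% |
| 10% | 25 | 77.5% | 25/137 = 18.2% |
| 20% | 22 | 72.9% | 22/134 = 16.4% |
| 30% | 20 | 69.3% | 20/132 = 15.2% |
| 50% | 14 | 55.6% | 14/126 = 11.1% |

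The removal fractions are assumptions, not figures from the article.

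**The case against.** The rule is permissive, and the follow-up section says that all subjects are followed. A reader might infer that the plan deletes patients who reach the endpoint. The article does not say so. If the serious event is itself a MACE, it has occurred and can be counted, and leaving afterwards costs a first-event analysis nothing. Such a case is lost only if the patient's data are also removed, and retention of data is a matter that the full protocol or analysis plan may settle. This stands: what the text itself exposes is mainly the censoring of patients with other serious events, or of non-compliers, before a later MACE.

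A reader might also infer serious bias in the plaque–MACE association. The simulation does not support that under censoring: the shift in log HR is small beside the sampling error from about 28 events.

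The loss figures assume that every patient with another serious event is excluded, which no section says. They also start from the 140 left after planned drop-out. The article does not say that exclusions fall outside that 20%, so some loss may be counted twice. This stands too, and makes the figures upper bounds for their scenario.

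Finally, VH-IVUS before and after PCI is a study procedure, so non-compliance or a peri-procedural event can leave a patient without usable imaging. Such a patient cannot enter the plaque models, and the repair has to allow for that. It is no reason to stop collecting outcomes that a telephone call can supply.

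**Conclusion.** The point holds as one of avoidable, outcome-related censoring. The article states a discretionary rule whose trigger overlaps the primary endpoint, and that rule contradicts its own statement on follow-up. Outright loss of endpoint cases follows only if excluded patients' data are removed, which the article neither says nor rules out.

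The actual size cannot be known without an exclusion rate. The censoring results in the table rest on the assumed event incidence, hazard ratio and shared frailty, and on exclusion of every patient with another serious event. They are an illustrative upper bound, and with selective use the effect is close to nil. The sample size of 175 is not in question.

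**What to change.** Delete serious adverse events and poor compliance as reasons for exclusion from the study, and reconcile the Participants section with the Baseline assessment and follow-up section. State instead that:

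- every enrolled patient who has PCI is followed for MACE and vital status to 36 months, by telephone where a visit is not possible;
- follow-up ends early only on death or withdrawal of consent, and all data and events to that date are kept;
- patients without usable VH-IVUS stay in follow-up and in the incidence estimates, and are reported separately from the plaque–MACE models.

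This changes one rule and needs continued telephone contact for a few patients; the sample size is unaffected. The Trial status section reports 67 participants enrolled by August 2018, with recruitment ongoing, so at that date an amendment could still cover most of the cohort.

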### Evaluation of the coronary angiography

Coronary angiography is performed using angiography system with a flat-panel detector (Philips Allura Xper FD10, Philips Healthcare, Netherlands) according to the Judkins technique. Angiography of the in situ coronary artery is performed with 6F catheters through radial or femoral access, while Judkins R (JR) 4.0 is used as the first choice catheters for SVG angiography. The location of SVG is roughly determined according to previous CABG surgery procedure and it is displayed in at least two different projections. The presence of significant stenosis (≥50%) in at least one SVG is defined as SVGD.

### VH-IVUS examination and plaque classification

After administration of heparin (100 U/Kg) and glyceryl trinitrate (100–200 μg), VH-IVUS is performed in SVG and other main coronary arteries before and after PCI. Data is obtained using a 20-MHz, 3.5-French EagleEye phased-array Gold catheter (Volcano Corporation, Rancho Cordova, California, USA) with motorized pullback (0.5 mm per second) from the most distal safe position to guide the catheter. The IVUS grey-scale and Virtual histology analyses are performed offline using the Volcano Image Analysis Software (version 3.0.394,Volcano Corporation, USA) and are not used for PCI guidance or subsequent management. Spectral and amplitude analyses of IVUS backscattered radiofrequency are performed by two experienced interventional cardiologists without knowledge of subsequent clinical events. Angiographic qualitative assessment and quantitative measurements are obtained for SVG. Quantitative IVUS measurements include cross-sectional areas (CAS) of the lumen, the external elastic membrane (EEM), and the plaque and media (EEM CAS minus lumen CAS), lesion length, plaque burden (plaque and media CAS divided by EEM CAS), and plaque volume. Qualitative IVUS assessments include plaque rupture (intraplaque cavity that communicated with the lumen with an overlying residual fibrous cap fragment) and characterization of lesions. On the basis of radiofrequency IVUS, plaque components and morphology are classified into the following four types: fibrous tissue (FT), fibrofatty (FF), necrotic core (NC), and dense calcium (DC). A lesion on IVUS imaging is defined as a plaque burden ≥40% in at least 3 consecutive frames. Consistent with published VH-IVUS classifications [25, 28], such lesions are classified as one of the following: 1) fibrotic plaque, mainly fibrous tissue with < 10% confluent NC, < 10% confluent DC, and < 15% FF; 2) fibrocalcific plaque (FCa), mainly fibrous tissue with > 10% confluent DC but < 10% confluent NC; 3) pathologic intimal thickening (PIT), not meeting FCa plaque definitions and predominantly fibrous tissue; 4) fibroatheroma, > 10% confluent NC, including thick-cap fibroatheroma (ThCFA) and thin-cap fibroatheroma (TCFA).

### Baseline assessment and follow-up

After receiving written informed consent, clinical staff will collect demographic and clinical characteristics from all participants. Medical records will be reviewed and related clinical information will be extracted. The data to be collected at baseline include demographic characteristics, medical history (diabetes mellitus, hypertension, hyperlipaemia, stroke, arrhythmia, previous myocardial infarction, PCI or CABG surgery, and medicines for cardiovascular disease), physical examination, clinical presentation (vital signs at hospital admission, onset time of chest pain, duration of chest pain, cardiac function with Killip classification), and smoking history. Cardiac color ultrasound, coronary angiogram, pre- and post-PCI VH-IVUS and 18 lead ECG will be done and used for checking inclusion/exclusion criteria. In addition, blood samples will be collected for laboratory testing, including routine blood, blood biochemistry, fasting glucose, coagulation function, homocysteine, cardiac damage markers (lactic dehydrogenase, creatine kinase, B-type natriuretic peptide, hydroxybutyrate dehydrogenase, troponin H, myoglobin), and inflammatory factors.

Eligible participants will be hospitalized for PCI treatment. In the therapy phase, patients will receive PCI for SVGD using drug-eluting stents. Operation notes (operation date, bleeding volume, medication), thrombolysis in myocardial infarction (TIMI) flow, corrected TIMI frame count (CTFC) and adverse events will be recorded in detail.

All subjects will be followed up at 1, 6, 12, 24 and 36 months after surgery, with MACEs and adverse events assessment collected at each time by clinic visits or telephone interview.

